#### Missing outcome data

EHR data are shown to be almost complete for mortality.^19^ Patient deaths missing from EHRs are expected to be missing at random equally in both treatment arms, thereby not altering the overall direction of treatment effect. The classification of unspecified stroke type will cause uncertainty in the main safety endpoint and may lead to a lower event rate for major bleeding compared with the trial; this would affect the power but should not affect the treatment effect seen as events are expected to be missing at random from both treatment arms.

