#### ARISTOTLE

ARISTOTLE was a randomised, double-blind trial completed in 2011, comparing apixaban with warfarin in the prevention of stroke and SE. The trial included 18 201 patients with AF and at least one additional risk factor for stroke. The trial was designed to test for non-inferiority of apixaban compared with warfarin, and showed apixaban superiority for (1) the primary outcome of stroke or SE (HR 0.79, 95% CI 0.66 to 0.95),^7^ (2) the safety endpoint of major bleeding (HR 0.69, 95% CI 0.60 to 0.80), and (3) death from any cause (HR 0.89, 95% CI 0.80 to 0.99). The ARISTOTLE findings led to the National Institute for Health and Care Excellence (NICE) guidelines on stroke prophylaxis in patients with AF recommending apixaban as a treatment. Baseline patient characteristics from ARISTOTLE will be used in selection of participants in Objective 1.

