#### Outcomes

Outcomes to be measured are as follows:

Stroke (ischaemic or haemorrhagic) or SE.Major bleeding.MI.All-cause mortality.Time to AF treatment change.

Outcomes will be ascertained using a combination of CPRD, HES and ONS data.

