### Statistical analysis

#### Methods of analysis

ARISTOTLE used an intent-to-treat (ITT) approach for the primary efficacy analysis and an on-treatment approach for sensitivity analysis and safety outcomes. We will perform equivalent analyses by using two different censoring schemes: a primary censoring scheme censoring 5 years after index date (reflecting the maximum possible follow-up in ARISTOTLE) for the primary effectiveness analyses, and an on-treatment scheme censoring around time of last study drug for the sensitivity analysis and safety outcome. For the on-treatment censoring scheme, date of last exposure will be estimated using patient prescription data—to allow for drug half life, stockpiling of tablets and less than 100% adherence we will add 30 days after the apparent end of treatment.

Demographic and baseline variables will be presented before and after matching steps. As the primary analysis accounts neither for treatment switching nor discontinuation, the proportion of patients discontinuing treatment and time to treatment discontinuation will be tabulated.

The primary effectiveness endpoint is time to first occurrence of confirmed stroke (ischaemic, haemorrhagic or unspecified type) or SE during the study, regardless of whether the subject is receiving treatment at the time (primary censoring scheme). Comparisons will be made according to prescribed treatment (apixaban vs warfarin).

All time to event endpoints will be analysed using a Cox proportional hazards model including treatment group as a covariate and prior warfarin/VKA status (experienced, naïve). Point estimates and two-sided 95% CIs will be constructed for the outcome. Absolute event rates of all outcomes of interest will also be calculated.

Secondary outcomes cover the key safety outcome of major bleeding and the individual outcomes of stroke, SE, MI and mortality. Secondary outcomes other than major bleeding will use the ITT censoring scheme, major bleeding will use the on-treatment censoring scheme.

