#### Validation of observational results against ARISTOTLE data

In Objective 1 alone, we will validate the findings from our primary analysis against ARISTOTLE by determining whether results are compatible with the trial results. ARISTOTLE demonstrated superiority of apixaban over warfarin for the primary endpoint (HR 0.79, 95% CI 0.66 to 0.95).^7^ The treatment effect seen with EHR data may be weaker than that seen in ARISTOTLE.

An analysis of EU patients in ARISTOTLE showed a smaller treatment difference for the primary endpoint and death: HR for stroke/SE 0.92 (95% CI 0.56 to 1.52), all-cause death 0.89 (95% CI 0.68 to 1.18). The European Medicines Agency Assessment Report suggested the smaller treatment effect may have been due to superior INR control in the warfarin arm of the EU subgroup (median time in therapeutic range (TTR) 68.93%)^15^; this study could provide additional evidence on this point.

Either a result of superiority or non-inferiority will be considered compatible with ARISTOTLE results. We have set two criteria that must be met to conclude results are consistent with the trial result:

The effect size must be clinically comparable with the ARISTOTLE findings; the HR for time to stroke/SE with the EHR must be between 0.69 and 0.99. This range is not symmetrical around the ARISTOTLE estimate of 0.79 as it is anticipated the treatment effect in routine clinical care may be weaker than that seen in the optimised setting of a clinical trial.The upper limit of the 95% CI for the rate ratio must be less than 1.52 (upper limit in the EU subgroup of ARISTOTLE).

In addition, if the upper limit of the 95% CI is less than 1 then superiority of apixaban versus warfarin will be concluded.

In order to understand the extent to which the EHR population resembles the ARISTOTLE trial population the absolute event rates of the outcomes will be compared.

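### Losing haemorrhagic strokes to an unspecified code at random in both arms leaves the major-bleeding HR unchanged only if those strokes share the HR of the other major bleeds

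*Protocol article*

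**What the plan says.** The Missing outcome data section of the protocol article states: "The classification of unspecified stroke type will cause uncertainty in the main safety endpoint". It adds that this "may lead to a lower event rate for major bleeding compared with the trial". This implies that haemorrhagic stroke counts towards major bleeding and that some haemorrhagic strokes will be missed because their type is not recorded. The section accepts a cost in power, but says the loss "should not affect the treatment effect seen as events are expected to be missing at random from both treatment arms".

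The reference result, in the ARISTOTLE section, is "the safety endpoint of major bleeding (HR 0.69, 95% CI 0.60 to 0.80"). Under Methods of analysis, major bleeding is the key safety outcome, analysed by Cox regression with on-treatment censoring.

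The stroke outcome is worded in two ways. The Outcomes list has "Stroke (ischaemic or haemorrhagic) or SE". Methods of analysis defines the primary endpoint as "confirmed stroke (ischaemic, haemorrhagic or unspecified type) or SE".

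**The concern.** Loss that is equal in both arms protects an HR when it is also random across the events that make up the endpoint. By the protocol's own mechanism it is not random in that sense: haemorrhagic strokes can drop out of major bleeding through an unspecified stroke code, and other major bleeds cannot. Equal loss leaves the HR for haemorrhagic stroke as it was, but gives that component less weight. The composite HR then moves towards the HR of the bleeds that remain.

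At stake is the reading of the key safety result. If the EHR bleeding HR differs from 0.69, part of the difference could come from stroke coding, and the current wording tells the reader to discount that explanation. The same outcomes are carried into the excluded patient groups (Objective 2) and the comparisons with rivaroxaban and dabigatran (Objective 3). Component shares and HRs may differ there, so a shift seen in Objective 1 need not carry over.

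**Working it through.** The plan gives no figure for this point, so there is nothing to reproduce. The check asks when the stated conclusion is true and how far it could be out.

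**Input from the document.** Composite major-bleeding HR 0.69, 95% CI 0.60 to 0.80 (ARISTOTLE section).

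**Assumptions, none given in the document.**
- *s*: haemorrhagic-stroke share of warfarin-arm major bleeds, 10-30%.
- *m*: fraction of haemorrhagic strokes lost to unspecified type, equal in both arms, 25-50%.
- *HR_h*: HR for haemorrhagic stroke, 0.4-0.6 as the main range. Values of 0.69 and above are added to test direction.

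**Formulas (rare events).** The full composite must equal 0.69, so

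HR_rest = (0.69 − s·HR_h) / (1 − s).

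After the loss,

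HR_obs = [s(1 − m)·HR_h + (1 − s)·HR_rest] / (1 − s·m).

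Substituting the first into the second gives

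HR_obs = (0.69 − s·m·HR_h) / (1 − s·m),

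so the shift is s·m·(0.69 − HR_h) / (1 − s·m). It is zero only if nothing is lost or HR_h = 0.69, and its sign depends on whether HR_h lies below or above 0.69.

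| s | m | HR_h | Calculation | HR_obs |
|---|---|---|---|---|
| 10% | 25% | 0.6 | (0.69 − 0.015)/0.975 | 0.692 |
| 10% | 25% | 0.5 | (0.69 − 0.0125)/0.975 | 0.695 |
| 20% | 50% | 0.5 | (0.69 − 0.05)/0.90 | 0.711 |
| 30% | 50% | 0.4 | (0.69 − 0.06)/0.85 | 0.741 |
| any | any | 0.69 | 0.69(1 − s·m)/(1 − s·m) | 0.690 |
| 10% | 25% | 1.0 | (0.69 − 0.025)/0.975 | 0.682 |
| 20% | 50% | 1.0 | (0.69 − 0.10)/0.90 | 0.656 |
| 30% | 100% | 0.4 | (0.69 − 0.12)/0.70 | 0.814 |

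The first and fourth rows are the ends of the main range: 0.692 to 0.741. The last row takes every extreme at once, including loss of all haemorrhagic strokes, and is the only row outside the trial's interval.

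**Event rate.** The warfarin-arm bleeding rate falls by s·m: 0.10 × 0.25 = 2.5% to 0.30 × 0.50 = 15%.

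**Stroke wording.** The Outcomes list does not name unspecified type; the primary endpoint definition does. If an analyst dropped unspecified strokes, with an assumed 20% share of stroke/SE events, 0.79 would become (0.79 − 0.2 × 0.6)/0.8 = 0.84 if their HR were 0.6, and (0.79 − 0.2 × 1.0)/0.8 = 0.74 if it were 1.0. Both stay inside the validation range of 0.69 to 0.99.

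**The case against.** The strongest reply is that the error is conditional and small. The document gives no component HR, share or unspecified fraction, so no bias can be shown from it. A reader might infer that the statement is simply false, or that coding loss will make apixaban's bleeding benefit look weaker. Neither follows. Equal component HRs would make the statement exact, and the upward direction in the main range comes from assuming HR_h below 0.69. At 25-50% loss the whole main range stays within 0.60 to 0.80. This all stands, and it limits the point to a missing condition.

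The text is also hedged. It speaks of expectation, admits uncertainty in the safety endpoint and discloses the lower event rate. It does not claim that bias is impossible, and should not be read so. Even so, the reason it gives does not support its conclusion.

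Nor does the validation decision depend on major bleeding: the criterion is "the HR for time to stroke/SE with the EHR must be between 0.69 and 0.99", with a limit on the upper confidence bound for the same outcome. That is correct.

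A reader might infer from the two stroke definitions that the validation event set is undefined. It is not. Methods of analysis gives the operative definition of the primary endpoint and includes unspecified type; the Outcomes entry is a short list. Counting such strokes in stroke/SE but not as bleeds is no contradiction either.

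Finally, sensitivity analyses for outcome coding may sit in a fuller document that is not shown, so their absence here is not the finding. The finding is an inference that the article states and that lacks its condition.

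**Conclusion.** The point holds in conditional form. Random, equal loss preserves the major-bleeding HR only if haemorrhagic stroke and the remaining major bleeds have the same HR, and the article neither states nor supports that condition. Under the assumed main range, 0.69 becomes about 0.69-0.74, a shift of roughly 0.00 to 0.05. The shift is zero at equal HRs and negative if HR_h exceeds 0.69. These figures rest on rare events, equal loss in both arms and assumed values of all three inputs, and on haemorrhagic stroke being part of major bleeding, which the text implies. The consequence is for interpreting the key safety HR, not for the Objective 1 validation test. The stroke definitions need only a wording alignment.

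**What to change.** 1. In Missing outcome data, replace the claim that the treatment effect is unaffected. Say that it is unaffected only if haemorrhagic stroke and the other major bleeds have the same HR, and that otherwise the composite HR moves towards that of the bleeds still captured.
2. Add two sensitivity analyses of major bleeding, using the same Cox model and on-treatment censoring:
   - **(a)** Exclude all haemorrhagic and unspecified strokes in both arms. Compare with ARISTOTLE only with the caveat that the endpoint differs. Do not label it extracranial bleeding only unless other intracranial bleeds are also removed.
   - **(b)** Count unspecified strokes as bleeds. Label this an extreme scenario, because it brings in ischaemic strokes.
3. In the Outcomes list, add *or unspecified type* to the stroke entry to match the operative primary endpoint definition.

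The cost is a few words and two re-runs of an existing model; no new data are needed. If the HRs from (a) and (b) lie close to the main estimate, stroke coding is an unlikely explanation for a difference from the trial. If they do not, the reader can see how far the result depends on it.

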#### Limitations of the study design, data sources and analytical methods

Some of the criteria assessed for ARISTOTLE eligibility may not be well recorded in CPRD, criteria such as alcohol and drug abuse may not be captured for all patients. For criteria such as ‘increased bleeding risk’, it is unclear which codes to include and timescale to consider. These limitations are consistent with our aim to select a population as similar as possible to ARISTOTLE while acknowledging differences will remain. The most important risk factors for the primary outcome of stroke (the components of CHA2DS2-VASc score for AF stroke risk) are mostly well recorded in CPRD.^20^

There are differences in the coding systems used by the two EHR data sources and completeness of coding may differ between the two; the potential impact of this will be ascertained by comparisons of rates of diagnoses, baseline variables and prescriptions of interest. Inclusion of data source as a matching variable should prevent discrepancy between the sources from biasing results. We will explore different methods of combining Gold and Aurum, namely analysing separately by database and combining the results as a meta-analysis as an alternative to combining data before analysis.

The main focus of the study is validation of our methodology through assembling a cohort of patients comparable to the patients in ARISTOTLE and finding similar results to the trial. Criteria to determine the success of the methodology have been prespecified in the protocol. Given the use of CPRD data to determine treatment effectiveness is not yet well established, a finding that these data are not suitable to answer questions on intended effectiveness will be a useful conclusion.

### Patient and public involvement

No patient was involved.

## Ethics and dissemination

### Approval by ethics and scientific committees

An application for scientific approval related to use of CPRD data was approved by the Independent Scientific Advisory Committee of the Medicines and Healthcare Products Regulatory Agency (MHRA).

### Dissemination plans

The results of the study will be submitted to peer-reviewed journals and presented at conferences. Relevant charities will be contacted for guidance on dissemination of results to patients in an accessible manner. We will communicate with NICE to convey any results relevant to the guidance they have issued on AF, and with the MHRA if findings may impact the risk/benefit profile of anticoagulation treatments in patients with AF.
